## Discussion

One of the strengths of our study is that it has been designed to minimize disruption for the participants since the data collection points have been timed to coincide where possible with routine clinic visits and home visits. According to the health policy in China, the maternity leave is 98 days. During this time, the majority of mothers will practice a traditional postpartum confinement at home and keep routine contact with the community clinic where they are registered. In Beijing, most community clinics will schedule a routine home visit at one week postpartum for all registered mothers. Hence, the baseline assessment of this study is scheduled at one week postpartum when the trained clinic nurses conduct their routine home visit. Thus our baseline assessment and data collection can be conducted during their routine home visit to reduce imposing an extra interruption and additional burden on the mother. Moreover, since there is a routine contact, the nurse can provide the scale and the eight week questionnaires during the contact one week prior to the eight week data collection. Mothers can fill in the questionnaires using their leisure times and return the scale and questionnaires when they take their infant to the clinic for the second month vaccination; the nurse can also conduct the eight week sample collection and infant anthropometry measurement during the time when mothers bring their infants to the clinic for vaccination. These routine contacts with local clinics should help to reduce the potential attrition rate.

In the MOM study [10], the milk intake was measured by the stable isotope method (deuterium dilution). However, the local investigators thought that this would discourage Chinese mothers from participating. Hence, we elected to use the conventional 48-h test-weighing method for the measurement of milk intake, by calculating the difference between the infant’s weight immediately before and after each breastfeeding during a 48-h period. Data will be adjusted for any extra water consumed, water derived from oxidation of milk macronutrients, and water stored in fat and protein (calculated from body water and weight change and published values for protein and water contents of lean body mass) during analysis. A previous study compared the accuracy of test-weighing and the stable isotope method, and showed no significant difference between the two methods by paired t-test [35]. However, both methods might have potential sources of error. The calculation of water output depends on the assumption that the mean loss of water subject to fractionation applies to all infants. A mean value based on recent data in Chinese infants will be used to reduce the bias. Moreover, based on previous research, a 100% error in this figure will only result in 1% error in water output [35].

To control for the influence of antibiotics on maternal gut and milk microflora, the assessment of microbiota will be conducted in mothers who were vaginally delivered their infants, since the delivery mode has been shown to influence infant’s gut microbiota. We will also record the antibiotic use of all mothers and infants at the baseline and follow-up assessments. While the microbiota can be influenced by maternal diet, this would be expected to be balanced between treatment group and control group.

In summary, this study aims to show causal relationships between maternal psychological state and breastfeeding outcomes, which may mediate infant behaviour and the gut microbiota. To our knowledge, the present study will be the first RCT that investigates the role of HMO and microbiota in mother-infant signalling. Findings of this study may identify modifiable factors which can be used to encourage and support exclusive breastfeeding.

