#### Test-weighing

For the measurement of milk intake, researchers will lend a digital electronic infant weight scale to mother for 48 h and mother will be asked to weigh her infant right before and right after a feeding, and the duration between the two weight measurements will be recorded to adjust for insensible water loss. Care will be taken to ensure that the infant is weighed with the same clothing before and after the feed. The difference in weight, adjusted for insensible water loss during the feeding period, is the amount of breastmilk the infant consumed during the feeding.

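### The Discussion applies isotope water-balance adjustments to test-weighing data, which contradicts the Test-weighing section and does not fit the measurement

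*Protocol article*

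**What the plan says.** The Test-weighing section (under Other assessments) has the mother weigh the infant just before and just after each feed for 48 hours. It says that "the duration between the two weight measurements will be recorded to adjust for insensible water loss" and then defines the result: "The difference in weight, adjusted for insensible water loss during the feeding period, is the amount of breastmilk the infant consumed during the feeding". No other correction appears there.

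The Discussion explains that the earlier Malaysian study used deuterium dilution and that local investigators expected this to put Chinese mothers off. "Hence, we elected to use the conventional 48-h test-weighing method for the measurement of milk intake", it says, and it restates the before/after weight definition. The next sentence reads: "Data will be adjusted for any extra water consumed, water derived from oxidation of milk macronutrients, and water stored in fat and protein". The stored water is to be "calculated from body water and weight change and published values for protein and water contents of lean body mass". After remarking that both methods may have error, the paragraph continues: "The calculation of water output depends on the assumption that the mean loss of water subject to fractionation applies to all infants". It then adds: "A mean value based on recent data in Chinese infants will be used to reduce the bias". Insensible water loss is not mentioned in the Discussion.

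Increased milk volume is part of a secondary hypothesis. Milk energy at eight weeks is a listed secondary outcome, calculated from test-weighed intake. The Statistical analysis plan section compares changes in milk volume and energy between arms by two-sample t-test.

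**The concern.** One measurement has two adjustment rules. The rule in Methods suits test-weighing. The rule in the Discussion is built for a method that this trial says it is not using.

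An isotope method measures water turnover and has to convert it into milk. It must therefore take account of water from other sources, water made by metabolism, water retained in growth, and isotope fractionation. Test-weighing reads the mass of milk directly and needs no such conversion.

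An analyst who followed the Discussion would add to or subtract from a direct mass measurement amounts that do not belong there. That would misstate milk volume and the energy calculated from it. If the two rules are reconciled only once data are in hand, the choice becomes a post-hoc decision on secondary outcomes.

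**Working it through.** No stated figure is in dispute, so the main check sets the two rules side by side.

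| Term | Test-weighing section | Discussion | Applies to a before/after-feed weight difference? |
|---|---|---|---|
| Insensible water loss | Yes, from the recorded interval | Not mentioned | Yes |
| Extra water consumed | Not mentioned | Yes | Only if given between the two weighings of a feed |
| Water from macronutrient oxidation | Not mentioned | Yes | No: it is not swallowed in the feed, and what evaporates is already insensible loss |
| Water stored in fat and protein | Not mentioned | Yes, from body water and weight change | No, and no body-water measurement is described |
| Water output and fractionated loss | Not mentioned | Yes, with a mean value to be used | No: there is no isotope to fractionate |

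**Can the Discussion rule be carried out?** The sections on anthropometry, test-weighing, milk samples and stool samples describe no isotope dose and no body-water measurement. The storage and fractionation terms therefore cannot be calculated from the data described. The oxidation term could be attempted, because fat, protein and carbohydrate are measured in milk.

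**Ceiling for the oxidation term.** All inputs here are assumptions, not document figures: milk with 3-4% fat, 6.5-7% carbohydrate and 1-1.2% protein; metabolic water of 1.07, 0.58 and 0.41 g per g; every gram oxidised.

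Water per 100 g milk = 1.07 × fat + 0.58 × carbohydrate + 0.41 × protein

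- 3.0 / 6.5 / 1.0: 3.21 + 3.77 + 0.41 = 7.39 g
- 3.5 / 7.0 / 1.0: 3.745 + 4.06 + 0.41 = 8.22 g (rounded)
- 4.0 / 7.0 / 1.2: 4.28 + 4.06 + 0.492 = 8.83 g

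This gives about 7-9% of volume as a maximum for this one term. It scales with the fraction oxidised: at one half it is 3.7-4.4%. The net of all terms cannot be derived.

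**Effect on the comparison of arms.**

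- *Same proportion c removed from everyone.* Each value becomes (1 − c) times itself. The mean difference and its standard error both shrink by (1 − c), so t does not change. In a simulated example with c = 10%, t was 2.18 before and after. Absolute volumes and energy would still be wrong.
- *Term based on weight change.* The shift in the arm difference is k × (difference in daily gain). With an assumed 2-10 g/day difference and k of 0.5-1.0, it runs from 2 × 0.5 = 1 to 10 × 1.0 = 10 g/day. Against an assumed intake of 400-800 g/day, that is 1/800 = 0.1% to 10/400 = 2.5%.

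**The case against.** The best reply is that Methods already defines the measurement correctly and collects the interval it needs. The outcome list and the analysis section add no other adjustment. The disputed text sits in a Discussion paragraph that justifies a change of method, and its remark that both methods have errors suggests that the fractionation sentence is comment on the isotope approach.

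Part of this stands. The conflict is between Discussion and Methods, and the fractionation sentence can be read as commentary. The paragraph also says that even a 100% error in the fractionation figure would change water output by only 1%. The adjustment sentence is harder to excuse. It comes before the remark on both methods, follows directly on the description of test-weighing in this trial, and is in the future tense. So is the sentence on the mean value for Chinese infants. If commentary was meant, the text still needs to say so.

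A reader might infer that milk volumes will be wrong by 7-9%. The documents do not support that. The figure rests on outside values and complete oxidation, whereas the same sentence allows for water stored in tissue.

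A reader might also infer that an effect on growth would create or hide a difference in milk volume. That route exists only if the storage term is applied. The term cannot be computed from the data described, and nothing shows that 1-10 g/day would matter against a plausible effect or standard deviation.

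**Conclusion.** The point holds as a contradiction and as a wrong rule for this measurement. The Discussion commits test-weighing data to water-turnover adjustments that do not apply to a weight difference, and Methods adjusts only for insensible loss.

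If the Discussion rule were applied, milk volume and the energy derived from it would be misstated. The size is unknown: the only figure available is an assumption-based ceiling of about 7-9% for the oxidation term. A correction in a common proportion would not alter the test between arms. A weight-change term could, if growth differs, but its size is only illustrated here under assumed inputs.

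The primary outcomes (stress, anxiety, infant weight and length gain), the sample size and data collection are unaffected. It would be too strong to call the measurement itself mis-specified or the trial's main conclusions threatened. This is a lower-level correction to secondary outcomes.

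**What to change.** 1. Make the Test-weighing section the single definition: milk intake is the sum over 48 hours of after-feed minus before-feed weight, adjusted for insensible water loss from the recorded interval, in the same way in both arms.
2. In the Discussion, delete the oxidation, storage, water-output and fractionation text, or state that it describes the isotope method only.
3. Keep an extra-water subtraction only for water given between the two weighings of a feed. Removing it altogether would leave that water counted as milk.
4. Have the sponsor state what the Chinese-infant mean value is. The Discussion ties it to fractionated water loss, so the text gives no ground for using it as an insensible-loss rate until that is clarified.

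The cost is a text correction, with no change to data collection as described. It should be made before milk volume is analysed.

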**Discussion:**

Primary outcomes of this study will be the effect of the intervention on maternal psychological state, and infant growth. Other outcomes will include the effect of the intervention on milk production, infant behaviours, and the microbiome composition in breastmilk and maternal and infant’s gut. Results of this study will provide greater understanding about maternal-infant factors which influence the success of breastfeeding, and which may then be useful targets for future interventions.

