#### Secondary hypotheses

The use of a relaxation therapy by breastfeeding mothers of LPI and ETI from one week to eight week postpartum will result in increased breast milk volume, energy carbohydrate and total amount of HMO in breast milk.The use of a relaxation therapy by breastfeeding mothers of LPI and ETI from one week postpartum will have a positive effect on maternal attitudes toward breastfeeding and infant eating behaviour.The composition of microbiome in vaginally delivered infant’s gut and their mother’s milk is associated, and this will be altered by the intervention, with effects on infant appetite, behaviour and temperament.

Secondary outcomes and measures
energy content of breast milk at eight weeks, calculated by milk intake assessed using test weighing methods [21].composition of macronutrients, specifically the lactose and HMO in breast milkcomposition of breast milk microbiota, maternal and infant gut microbiota, measured by the 16S rRNA based amplicon sequencing techniqueinfant appetite at eight week, three month, and six month, assessed using the Baby Eating Behaviour Questionnaire (BEBQ) [22].maternal feeding attitudes at eight week, three month, and six month, measured using the IOWA Infant Feeding Attitudes Scale (IIFAS) [23].infant behaviour, measured by three day infant behaviour diary at eight week.

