### Statistical analysis plan

All questionnaires and anthropometric data will be analysed using IBM SPSS (version 24). Intention-to-treat analysis will be performed for comparing primary outcomes (perceived stress and anxiety, infant weight and length gain from baseline to the endpoint) between intervention and control groups at the eight week postpartum using two sample t-test. Paired t-test will be used to compare baseline to post-intervention changes of each primary outcome. The association between the effects of the intervention and the frequency of use will be examined by two-tailed Pearson correlation. Two-sample t-test will be used to compare the changes in milk volume, energy and macronutrients level between intervention and control group. Regression analysis will be used to adjust for confounding factors.

Furthermore, associations between infant temperament/behaviour and the composition of microbiota in mother’s breastmilk, mother and infants’ gut will be examined using univariate ANOVA. Multiple regression analysis and MANOVA will be used to detect differences among significant predictor variables identified by ANOVA.

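### The behaviour–microbiota associations are planned without a term for randomised arm, although the arm may drive both sides; diet balance between arms does not protect them

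*Protocol article*

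**What the plan says.** The Statistical analysis plan section has two paragraphs. The first covers the comparisons between arms (stress, anxiety, infant growth, milk measures) and ends with "Regression analysis will be used to adjust for confounding factors". The second covers the microbiome. It announces tests of "associations between infant temperament/behaviour and the composition of microbiota in" breast milk, maternal gut and infant gut by univariate ANOVA, and continues: "Multiple regression analysis and MANOVA will be used to detect differences among significant predictor variables identified by ANOVA". Neither microbiome step names the randomised arm, a within-arm analysis or any covariate.

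The Secondary hypotheses section says of the microbiome that "this will be altered by the intervention, with effects on infant appetite, behaviour and temperament". Separately, it says that the intervention "will result in increased breast milk volume, energy carbohydrate and total amount of HMO in breast milk", and that it will favourably affect infant eating behaviour.

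The abstract makes the comparison of arms an aim as well: "Other outcomes will include the effect of the intervention on milk production, infant behaviours, and the microbiome composition".

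On diet, the Discussion says: "While the microbiota can be influenced by maternal diet, this would be expected to be balanced between treatment group and control group". It adds that antibiotic use will be recorded. No diet record appears in the text or in Table 2; Fig. 3, which details data collection at each visit, is not available here.

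**The concern.** Randomisation makes the two arms comparable. It does not make mothers with one microbiota profile comparable to mothers with another. When one outcome measured after randomisation is related to another, anything that affects both can create an association, however well the arms are balanced.

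Two such causes matter here. The first is the arm itself. If the intervention works as hypothesised, treated mothers and infants differ from controls in microbiota and may differ in infant behaviour through milk volume, energy or oligosaccharides. Analysed together without an arm term, the two groups form two displaced clouds, and the displacement alone is a correlation. The second is diet, which the article accepts as an influence on the microbiota. Its only stated reason for not pursuing diet is balance between arms, which does not bear on this analysis.

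At stake is how a secondary result is read. The article aims to explore the role of microbiota in mother–infant signalling. A behaviour–microbiota association could be taken as such a signal when part of it only reflects who received the recording.

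**Working it through.** **Inputs from the Sample size section.** Difference D = 3.13 and SD = 5.00 on the Perceived Stress Scale; 80% power; significance level 0.05; 120 infants; microbiome analysis in vaginal deliveries only, about 40%.

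**The plan's own figure.** N = 16 × SD²/D² = 16 × 25/9.797 = 40.83, so 41 per group and 82 in total. This reproduces, and the point does not depend on it.

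**Size of the microbiome set.** 120 × 0.40 = 48 pairs, about 24 per arm.

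**Correlation induced by the arm.** Suppose there is no link between microbiota and behaviour within either arm, the arms are equal in size, and the arm shifts each variable by d within-arm SDs. The between-arm part of the covariance is d²/4 and each total variance is 1 + d²/4, so

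r = (d²/4) / (1 + d²/4).

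The documents give no effect size for microbiota or behaviour. As a stand-in take d = 3.13/5.00 = 0.626 and vary it:

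| d (assumed, both variables) | induced r | rejection at nominal 5%, n = 48 |
|---|---|---|
| 0.3 | 0.0225/1.0225 = 0.022 | about 5% |
| 0.626 | 0.0980/1.0980 = 0.089 | about 9% |
| 0.8 | 0.16/1.16 = 0.138 | about 15% |
| 1.0 | 0.25/1.25 = 0.200 | about 29% |

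The last three rejection rates are simulated. The Fisher z approximation checks the second row: 0.0894 × √45 = 0.60, and P(Z > 1.36) + P(Z < −2.56) = 0.087 + 0.005 = 0.092. The same approximation gives the first row: 0.022 × √45 = 0.15, and 0.035 + 0.0175 = 0.05. A test of correlation stands in for the ANOVA, whose grouping the article does not define.

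**Effect of adding the arm.** In 20,000 simulated trials at d = 0.626 with no diet effect, the unadjusted association rejected in 9.0% and the arm-adjusted one in 5.1%.

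**Diet.** Let diet correlate c with both variables (an assumed range; the documents give no figure, and they link diet only to the microbiota). The induced r is c². Simulated rejection rates at n = 48:

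| c | arm shift | unadjusted | adjusted for arm | adjusted for arm and diet | comparison of arms on microbiota, diet ignored |
|---|---|---|---|---|---|
| 0.3 | 0 | 9.1% | 9.1% | 5.0% | 4.9% |
| 0.5 | 0 | 40.4% | 39.6% | 5.0% | 4.8% |
| 0.3 | 0.626 | 22.1% | 9.3% | 5.1% | not a null case |
| 0.5 | 0.626 | 60.7% | 40.0% | 4.9% | not a null case |

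The comparison of arms holds its 5% level with diet ignored, so the diet sentence is right there. The association does not. Adjusting for arm removes only the part due to the arm.

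**Timing.** Stool, milk and behaviour are recorded at one and eight weeks, and the microbiome paragraph does not say which visit it uses. The argument about the arm concerns the eight-week data. First-visit values cannot yet reflect use of the recording. The argument about diet applies to both visits.

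**The case against.** **The diet sentence is true as written.** It speaks of balance between the two groups, and the effect of the intervention on the microbiome is a stated aim. This stands. A reader might infer that the sentence is an error; it is not. The fault is that nothing limits it to the comparison of arms, while the microbiome analysis that is written out is an association.

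**Pooling over arms is inferred.** The article does not say in words that the arms are pooled or that the arm is left out. It has a general sentence on regression adjustment and a second, multivariable step, and covariate lists are often left to a fuller document. This stands in part. But the adjustment sentence closes the paragraph on arm comparisons, and the first microbiome step is fixed as a univariate screen that decides what enters the second. As written, the arm is not in the step that selects.

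**The hypothesis describes mediation.** The microbiome is to be altered, with effects on behaviour. If the intervention reached behaviour only through the microbiota, the arm would not confound. That is correct, but the other secondary hypotheses supply routes through milk volume, energy and oligosaccharides that need not pass through the microbiota.

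**The magnitude is borrowed.** The 0.626 SD is an effect on perceived stress, with no basis in the documents for microbiota or behaviour. This stands; it is an illustration, and smaller shifts induce almost nothing.

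**Chance imbalance.** A reader might also infer that 24 pairs per arm are too few to rely on balance of diet in the arm comparison. The documents do not support that as a defect: chance imbalance is ordinary sampling variation that the standard error already covers, and the simulated test held its level.

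**Conclusion.** The point holds in a limited form, and its place is the Statistical analysis plan section. The unadjusted behaviour–microbiota screen can return an association that the arm has produced. Under an assumed 0.626 SD shift in both variables the false rejection rate is about 9% in place of 5%, with r about 0.09; the larger figures above need larger assumed shifts or assumed diet correlations. The point rests on three conditions: the analysis uses eight-week data, the arms are analysed together, and the intervention has some path to behaviour other than the microbiota.

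Three stronger readings should be resisted. The article does not present these associations as its microbiome conclusion; it calls them associations, and they are secondary. The primary outcomes are untouched. And adjusting for arm would not remove confounding by diet, nor can it be said for certain that diet goes unrecorded, because Fig. 3 is not available.

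**What to change.** 1. In the Statistical analysis plan section, replace the univariate ANOVA screen with a regression model for each association that contains randomised arm and gestational-age stratum, and clinic if the degrees of freedom allow. All three are already held from randomisation. Delivery mode drops out because only vaginal deliveries enter. Do not add feeding status at sampling, which is itself measured after randomisation.
2. Report the results as observational, arm-adjusted associations.
3. In the Discussion, say that balance of diet applies to the comparison of arms only and that diet remains a possible confounder of the associations.

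Cost: wording, plus 1 degree of freedom for arm and 1 for gestational age, so 2; four clinics add 3, making 5, in about 48 pairs. The claim becomes more modest, and the diet problem is disclosed but not solved.

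Suggested text: *Associations between infant behaviour and microbiota will be estimated by regression including randomised arm and gestational-age stratum, and will be reported as observational.*
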